##### Questionnaires Included in Three and 6 Month Follow-Up Surveys:

ASI LiteCriminal JusticeWHOQOL-8Treatment Services ReviewMOUD Treatment Adherence and Satisfaction (MOUD)Pregnancy and Birth ControlPHQ-9

##### Qualitative Interviews

A random sample of consented participants are invited to complete a qualitative interview 3 months post release. We use the block randomization (block size of 3 from each sequential group of 10 consented participants). Semi-structured interviews with participants explore acceptability, patient-centeredness and satisfaction, including perceived utility of recovery mentor services, and barriers and facilitators to retention treatment. CRM and clinician interviews examine the implementation factors such as organizational setting, characteristics and implementation outcomes. All interviews are audio recorded, professionally transcribed and uploaded into a secure server for analysis. Interviews will last 60 minutes or less, and ROAR participants are compensated an additional 25 USD.

ROAR CRMs and clinicians are asked to complete qualitative interviews during the 18-month study period during work hours and are not compensated. Interviews will take place during the second half of program implementation.

##### Service Utilization Data

 Clinic staff abstract service utilization records from ROAR clinic sites documenting receipt of XR-NTX or other MOUD. Evaluation variables will include self-refort of engagement and retention in peer and SUD treatment services. CRMs log every interaction with participants, including reach-in visits, release visits, community meetings, phone calls, text messages and emails. The duration and purpose of each encounter is logged in REDCap using a structured tool.

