**Methods/design:**

In the week prior to their release, female adults in custody with moderate to severe opioid use disorder start treatment with extended release naltrexone, an injectable opioid antagonist that blocks the effects of opioids for up to 1 month. All ROAR participants receive training to use naloxone rescue kits and are provided nasal naloxone at release. Ongoing support from a certified recovery mentor to facilitate sustained engagement with treatment for substance use disorders begins in the month prior to release from prison and continues for 6 months in community. We evaluate the association between ROAR participation and the primary outcome of opioid overdose.

Using administrative data provided by the Oregon Department of Corrections and the Oregon Health Authority, we compare the odds of overdose among ROAR participants versus a comparison group of females released from prison during the study period. Evaluation activities in community includes survey and qualitative interviews for 6 months post release, as well as a review of clinic records to assess retention on medication among the pilot cohort (*N* = 100).

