Broadening scientific understanding about the feasibility and acceptability of XR-NTX to treat OUD among justice-involved women holds great public health significance. The ROAR pilot’s setting in an all-female prison will provide new information on barriers and facilitators of induction pre-release, as well as feasibility of retention on treatment in four Oregon counties in which local Medicaid covers treatment with all three forms of MOUD. Agency partners employ Certified Recovery Mentors (CRM) to facilitate transition to treatment post release. CRMservices are also billable to Medicaid in Oregon.

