#### Post-release procedures

##### SUD treatment in community

Participants are encouraged to engage in SUD treatment within the first 4 days of release and are followed by research staff and CRMs for 24 weeks. Participants may receive follow-up medical care, including any subsequent XR-NTX, buprenorphine or methadone, in community. Follow-up medical appointments within 1 week of release and any prior authorization for continued medication are part of release planning for ROAR participants. Subsequent XR-NTX injections are offered at the community treatment centers, and covered by Medicaid. The CRM engages with the participant prior to release and upon release to facilitate follow-up care. Participants are free to choose whether to continue XR-NTX or switch to opioid agonist therapy with buprenorphine or methadone following their release. Both participating treatment centers offer XR-NTX and buprenorphine on site, as well as either referral or delivery of methadone maintenance. The participant may also choose to discontinue medication treatment, while participating in outpatient or other counseling services.

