#### Follow-up Surveys

At 3- and 6-months post-release, participants are invited to complete a 30-minute face to face survey that collects information about medical status, employment/support status, alcohol and drug use, overdose experiences, family/social relationships, psychiatric status and mental health treatment, patient health questionnaire responses, quality of life, criminal justice involvement, treatment services review, and MOUD treatment adherence. The ROAR research coordinator records participant responses directly in REDCap. The survey meetings are conducted in person in a public place of the participant’s choosing.

Items include the ASI-Lite questions adapted for a 3-month timeframe and the overdose experience items. Quality of life is measured using the World Health Organization Quality of Life-8 . Items using previously tested language will capture overdose experience. Participants are compensated 25 USD for completing the 3-month survey and 50 USD for completing the 6-month survey. Information collected from surveys is not shared with law enforcement officials.

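### The record-based measure of retention on medication stops at the ROAR clinics, so medication received elsewhere is recovered only by self-report and retention on any MOUD may be understated

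*Protocol article*

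**What the plan says.** **Source of the measure.** The abstract (Methods/design) describes "a review of clinic records to assess retention on medication among the pilot cohort". The Service Utilization Data section says whose records these are: "Clinic staff abstract service utilization records from ROAR clinic sites documenting receipt of XR-NTX or other MOUD". Its next sentence adds a second source: "Evaluation variables will include self-refort of engagement and retention in peer and SUD treatment services".

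**Surveys.** The Follow-up Surveys section lists, among the topics asked at 3 and 6 months, "treatment services review, and MOUD treatment adherence". The section on participant retention and compensation makes clear that a woman can complete these assessments without attending any clinic.

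**Where medication may be received.** The section on SUD treatment in community states: "Participants are free to choose whether to continue XR-NTX or switch to opioid agonist therapy with buprenorphine or methadone following their release". It continues: "Both participating treatment centers offer XR-NTX and buprenorphine on site, as well as either referral or delivery of methadone maintenance". The Background notes that methadone is dispensed only by certified opioid treatment programs. The Study flow section says the two partner programs were chosen partly for their capacity to provide XR-NTX and buprenorphine; it does not mention methadone there.

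**Other data held.** Aim 2 uses Medicaid claims and encounters from the state. The inclusion criteria require each participant to authorize record abstraction and linkage to state administrative data. The Background says that in the pilot counties "local Medicaid covers treatment with all three forms of MOUD". The article describes using the claims for overdose only.

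**The concern.** The intervention treats a switch from XR-NTX to another medication as an acceptable course, so a woman who moves to methadone and stays on it is a treatment success. If she was referred out, the abstracted records have no dispensing entry for her. On receipt of medication she then looks the same as a woman who stopped, unless the survey supplies her status. Missing such women can lower a clinic-record retention figure but cannot raise it.

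The survey is a partial remedy. It is taken at two time points and is absent for women who cannot be reached. The article itself says that study retention and treatment retention share barriers, among them return to opioid use, transport costs and mistrust, so survey loss is unlikely to be unrelated to medication status.

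At stake is how Aim 1 describes continuation on medication, which the state intends to use in planning later programs with both agonist and antagonist medications.

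**Working it through.** **Step 1: the plan's own retention figure.** The preliminary enrollment section reports 86% retained among 42 women who accepted the first injection: 31 still active plus 5 who completed 6 months.

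(31 + 5) / 42 = 36 / 42 = 85.7%, which rounds to 86%.

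The figure reproduces, but it counts women still in the study. It does not count women on medication and is not a survey response rate. The article gives no figure for retention on MOUD.

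**Step 2: which treatment each source can see.**

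| Treatment after release | ROAR clinic records | 3- and 6-month survey |
|---|---|---|
| XR-NTX or buprenorphine at a partner center | yes | yes, if she responds |
| Methadone delivered by a partner center | yes | yes, if she responds |
| Methadone by referral to another provider | receipt not recorded | yes, if she responds |
| Any MOUD from another provider | receipt not recorded | yes, if she responds |

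The last two rows depend wholly on self-report. The documents point directly to the third row; the fourth is possible but less clearly signaled.

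**Step 3: how large the gap could be.** Let
- R = true share of women on any MOUD (not in the documents; assumed 30% to 70%),
- s = share of those women treated off site (not in the documents; assumed 5% to 30%),
- c = share of off-site treatment recovered by self-report (not in the documents; 0 for clinic records alone, 80% as an assumed favorable case).

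Observed retention = R × (1 − s × (1 − c)), so the shortfall = R × s × (1 − c).

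| R | s | Shortfall, c = 0 | Shortfall, c = 0.8 |
|---|---|---|---|
| 30% | 5% | 0.30 × 0.05 = 1.5 points | 1.5 × 0.2 = 0.3 points |
| 50% | 20% | 0.50 × 0.20 = 10 points (40% observed) | 10 × 0.2 = 2 points (48% observed) |
| 70% | 30% | 0.70 × 0.30 = 21 points | 21 × 0.2 = 4.2 points |

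The range is 1.5 to 21 points from clinic records alone, and 0.3 to 4.2 points if self-report recovers 80%. These figures show sensitivity to the assumptions; they do not estimate the bias in this study.

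**The case against.** The strongest reply is that clinic records are not the only source. Self-report is named in the same paragraph as the record abstraction, and a questionnaire on MOUD adherence and a treatment services review are given at months 3 and 6 without any clinic visit. A woman on referred methadone can report it. This stands, and it rules out the claim that retention is read from clinic records only. The gap that remains is women who do not respond, and the time between the two surveys.

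A reader might infer more than the article supports:

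- **That off-site switchers are coded as off medication.** No such rule is stated. A referring center may also hold a note of the referral or keep the woman in counseling.
- **That women will widely be treated elsewhere.** Inclusion requires willingness to establish care at the partner site, both centers give XR-NTX and buprenorphine on site, and methadone may be delivered by a center. The clear off-site route is methadone by referral.
- **That a comparison of the two programs would be distorted.** No such comparison is planned.
- **That every retention figure is affected.** The Study design section speaks of retention in the pilot, and the Implementation section places retention at months 3 and 6, the survey times. That outcome may be participant retention. The concern applies to retention on medication, for which the abstract names clinic records.

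It can also be said that rules for combining sources belong in a fuller protocol or analysis plan. That is fair, and the absence of a combining rule is not the point made here. The article does state which records are used, and those records do not cover a treatment route that the intervention allows.

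**Conclusion.** The concern holds in a limited form. The record-based measure covers ROAR clinic sites only, while women may move to methadone obtained by referral. MOUD received off site is missed by the records and recovered only through the 3- and 6-month self-report, which is absent for women lost to follow-up. Retention on any MOUD may therefore be understated.

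That it is understated, and by how much, cannot be established from the documents, because they give neither the true retention nor the off-site share. The illustrative ranges rest entirely on the assumed R, s and c. The larger values require that self-report contribute nothing, which is not what the article plans.

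This is an Aim 1 matter. It does not touch the primary overdose outcome or the power table. It is an inexpensive improvement to a stated measure.

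**What to change.** Define retention on medication as receipt of any MOUD (XR-NTX, buprenorphine or methadone) from any provider. Determine it from ROAR clinic records together with MOUD claims in the Medicaid data already linked for participants, with self-report as a further source. At months 3 and 6, report the shares of women on XR-NTX, on an agonist, and with no MOUD found in any source. Keep the clinic-only figure, but label it as retention at a ROAR clinic.

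The cost is one changed definition and extra fields in the claims request; the article describes that request for overdose only, so the MOUD fields would have to be added. Some substance-use treatment claims may be restricted from release. Claims also miss months without Medicaid cover, a gap the article already anticipates for overdose by adding hospital discharge data. Clinic records and self-report remain as back-up for those months.

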##### Limited Administrative Dataset

Fatal and non-fatal opioid overdoses will be assessed for all women released from prison during the 18 month study period (expected *n* = 1000) regardless of participation in ROAR. Using administrative data provided by the Oregon Department of Corrections and the Oregon Health Authority, study staff will compare odds of overdose among ROAR participants (expected n = 100) versus a comparison group of at least 100 previously incarcerated adult women with a documented SUD who are released into Oregon counties that are not participating in ROAR. Multivariate statistical analyses will be conducted to adjust for county and patient level cofounders including level of substance abuse and mental health treatment needs assessed at intake.

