The burden and adverse consequences of substance use disorders (SUD) are substantially higher in the female inmate population compared to males. In 2016, 25% of incarcerated women were convicted of a drug offense compared to 15% of incarcerated men (Carson, Mueller, & Kaeble, 2018). Compared to men, incarcerated women are significantly more likely to have severe substance abuse histories, co-occurring mental disorders and physical health problems, and histories of trauma and abuse (Rettinger & Andrews, 2010; Van Voorhis, 2012; Van Voorhis, Wright, Salisbury, & Bauman, 2010). In the United States, women in the criminal justice system are more likely than men to abuse and be addicted to heroin and opioids (Evans, 2015). According to prison intake data collected in the past two years, roughly half of women entering prison in Oregon used heroin, street methadone, or other opioids in the 12 months prior to incarceration. Incarcerated women who have a history of opioid-addiction are more likely than men are to inject opioids (Evans, 2015). Moreover, women in prison have higher HIV rates compared to men (Galea & Vlahov, 2002). Incarcerated women are more likely to use opioids daily and have increased risk for an opioid overdose post-release (Evans, 2015). Finally, women are more susceptible to overdose than men for biological reasons , including lower tolerance leading to both physical dependence and overdose with small quantities of substance (Springer, Biondi, Frank, & El-Bassel, 2020). Although each of these risks make women more susceptible to drug overdose post-incarceration (Binswanger et al., 2007), unique treatment needs post-release and gender specific treatments for OUD and recovery support for incarcerated women have not been well studied (Evans, 2015).

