Evaluate the effect of the ROAR pilot on opioid overdose among adult women released from prison. We evaluate the association between participation and the primary outcome of opioid overdose, including either a fatal or non-fatal overdose event. Fatal and non-fatal opioid overdoses are assessed for all adult females released from prison during the 18-month study period (expected *n* = 1000) regardless of participation in the ROAR intervention. Using administrative data provided by the Oregon Department of Corrections (e.g., dates of incarceration) and Oregon Health Authority (i.e., Medicaid claims and encounters), we compare the odds of overdose among participants versus a comparison group of previously incarcerated adult females with documented addiction or dependence in administrative records. Data from the comparison group will consist of de-identified administrative data for fatal and non-fatal overdoses in the state. The study will not directly recruit for this group. Statistical analyses adjust for county- and patient-level confounders including level of substance abuse treatment need and mental health treatment need assessed at prison intake.

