**Fig. 3 Fig3:**
[figure not shown]
Preliminary ROAR enrollment: first 7 months of 18-month recruitment cycle (2/10/2020)

Early recruitment and retention rates suggest the that ROAR pilot will successfully enroll and retain participants as planned. Of 150 adults in custody referred for prescreening interview by end of month 7, 93% were screened using an in-person interview guide. Table 3 summarizes reasons why 32 women in custody were excluded from pre-screening interview process. Of those who completed the pre-screen interview (n=140), 61 were eligible to enroll. At total of 51participants (84% of those eligible at pre-screen) were consented and enrolled into the pilot. Of the first 46 participants released from prison, 42 accepted the first injection of XR-NTX prior to release. Of those, 86% were retained as participants in community (31 still active, and 5 completed 6-month follow-up). Recruitment is planned for a total of 18 months.

**Table 3 Tab3:** Ineligibility for ROAR Pilot Project (First 7 Months Recruitment)

	Number
**Reasons ineligible for pre-screening, post administrative record review (multiple response)**	32
Detainers	14
Mental Health	10
Medical Concerns	6
Refused prior to being presented with information sheet	5
Special Housing	2
Change in Release Date	1
**Reasons Ineligible for Consent/Baseline, post Screening Interview (multiple response)**	79
Does not meet DSM-5 criteria for moderate to severe opioid use disorder	68
Not interested in obtaining treatment to cut back or quit opioid use or to prevent using opioids when released	68
Would not consider medication-based treatment for opioid use disorder	36
Not willing to take at least one evidence-based measure to avoid becoming pregnant	11
Chronic pain that requires ongoing treatment with opioid pain medicine	7
Release outside of target counties	5
Disqualified by prison health services	2
Planning on conceiving in the coming months	1

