#### Analysis

##### Opioid Overdose

The primary outcome, opioid-related overdose, is measured using administrative (Medicaid claims, hospital discharge data) and vital statistics. We use hospital discharge data to supplement Medicaid claims data in the event that participants lose or change Medicaid enrollment. The validity of administrative data to identify opioid-related overdose is high (sensitivity = 97%, specificity = 85%) (Green et al., 2019). We use Oregon vital statistics (death certificate data) to ascertain opioid-related fatalities. Oregon has a centralized medical examiner model which is known to provide more consistent and specific reporting of drugs implicated in fatalities (Buchanich, Balmert, Williams, & Burke, 2018; Warner, Paulozzi, Nolte, Davis, & Nelson, 2013).

Our primary analysis will examine the effect of pilot participation on the rate of fatal and non-fatal overdose events. We will calculate person-years of follow-up using the time between release date and subsequent death or study conclusion. Thus, women will contribute to calculations of person-years once they are released, except during subsequent incarcerations or after fatality. We will censor follow-up at the end of Quarter 10 or the date of incarceration if they were in prison as of this date. Our primary outcome (any opioid overdose) will be modeled as a rate with person-years as an offset variable.

We will employ either a mixed logistic model if the outcome turns out a non-rare event, or a mixed poisson model (with poisson approximation to binomial distribution) if the outcome turns out to be a rare event. The effect of ROAR participation will be examined by testing the slope coefficient (i.e., b1, see below) of the main treatment effect variable (ROAR participation yes/no) in the model. We will also adjust the treatment effect using covariates such as age, race/ethnicity, incarceration time, and mental health level of treatment need while incarcerated. We control for correlation due to clustering at county level by including a random effect (i.e., α, see below) in the model.

*Alternatively, the model described below is employed for our analysis:*

g[E(y|x)] = b0 + b1*ROAR,+b2*x + α, where g(.) is a link function (e.g., logit or log link), and b2 is a slope coefficient vector of adjusting covariates included in the model; α is the random effect account for county specificity.

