##### Sample Size and Power

Based on current release data, we expect to enroll approximately 100 participants over the 18-month recruitment period. At least 100 non-participating formerly incarcerated women with SUD released from prison over the same time period comprise our comparison group, which is built from Oregon state administrative data. Using Markov chain Monte Carlo simulation, the minimal detectable difference between ROAR and non-ROAR groups with 80% power, 5% type I error, and equivalent sample of *n* = 100 in each of the ROAR and non-ROAR groups was computed. It was assumed that varying baseline rates of post-release overdose ranging from 20% and 25% per year, based on data from Oregon Health Authority and the increased risk of overdose in similar populations as reported in the literature. Note that this power analysis has taken into consideration the correlation due to clustering within county level. There are a few scenarios of common correlation for clustering in practice that have been considered while performing the power analysis. Raw risk difference is defined as a raw difference (e.g., p1-p2), and relative risk difference is defined as (p1-p2)/p1.

In the Table 4, we summarize minimum detectable absolute differences with associated relative risks, accounting for varying assumptions about within-county clustering (i.e., correlation).

**Table 4 Tab4:** ROAR power analysis

Minimal detectable differences of post-release opioid overdose as absolute difference and relative risk				
	Baseline rate 20%		Baseline rate 25%	
ρ	Raw risk difference	Relative risk difference	Raw risk difference	Relative risk difference
0.0000	0.105	0.48	0.12	0.52
0.0050	0.115	0.43	0.125	0.50
0.0075	0.120	0.40	0.13	0.48
0.0100	0.120	0.40	0.135	0.46

Calculations assume equivalent sample size of 100 participants for each control and intervention groups, a minimum of 80% power, and alpha level of 5%

Programs that facilitate MOUD in correctional facilities have been previously shown to have a large effect on overdose mortality (RR = 0.4). Given the assumptions described, our pilot is sufficiently powered to detect treatment effects similar to what has been observed in other studies of MOUD delivery through the correctional system (Green et al., 2018).

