## Discussion

Oregon is well-positioned to successfully pilot and maintain a new model of pre-release linkage to MOUD and CRM services for incarcerated individuals. The state has a lengthy history of demonstrated support for peer mentor services and a network of more than 1,200 CRMs. Oregon Medicaid covers peer support services and has an established peer training and certification program overseen by Oregon’s addiction professional licensing board and an active peer professional association. In 2017, a statewide expert workgroup developed a peer supervision competency guide and a best practice guide for forensic peer specialists working with individuals with criminal justice involvement. Similar to many other states, however, standardized pre-release peer linkages have not been established for incarcerated individuals. In 2017, Oregon’s Governor Kate Brown established a statewide opioid taskforce with a focus on increased access to opioid agonist and antagonist therapy and overdose prevention. The taskforce sponsored a successful bill providing funds to study and address barriers to MOUD and strengthen peer recovery support programs. The legislation requires the Oregon Health Authority, Department of Corrections, and Department of Consumer & Business Services to collaborate to identify these barriers to MOUD.

 ROAR's pragmatic evaluation plan has a number of inherent limitations. Our analysis of opioid-related overdoses using administrative data is an observational cohort design. Although we use a concurrent comparison cohort of women with OUD released into non-ROAR counties as a comparison group, these women may systematically differ in ways related to our outcomes. We attempt to mitigate this limitation by using multivariable regression models to control for potential imbalance, but residual confounding may persist. We will be circumspect when reporting findings from this analysis and acknowledge this limitation.

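### ROAR women must have moderate or severe OUD, but the comparator is defined by any SUD in three sections and by OUD in a fourth; the SUD wording would dilute the opioid-overdose comparison

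*Protocol article*

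**What the plan says.** The inclusion criteria require every ROAR participant to meet DSM-5 criteria for moderate or severe OUD. The comparison group is described in four places in the protocol article:

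- Methods, Aim 2: "a comparison group of previously incarcerated adult females with documented addiction or dependence in administrative records".
- Limited Administrative Dataset: "a comparison group of at least 100 previously incarcerated adult women with a documented SUD", released to counties outside ROAR.
- Sample Size and Power: "At least 100 non-participating formerly incarcerated women with SUD released from prison over the same time period comprise our comparison group".
- Discussion: "we use a concurrent comparison cohort of women with OUD released into non-ROAR counties as a comparison group".

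The first three set no opioid criterion; the fourth does.

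On adjustment, Aim 2 and the Limited Administrative Dataset section name the level of substance-abuse treatment need and of mental-health treatment need at intake. The primary model under Analysis, Opioid Overdose, lists "covariates such as age, race/ethnicity, incarceration time, and mental health level of treatment need while incarcerated". No section names an opioid-specific covariate.

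**The concern.** The primary outcome is opioid overdose, so having OUD is a central prognostic factor. Under the SUD wording that factor differs between the groups by construction: every participant has moderate or severe OUD, and only some comparators do. A larger comparison group does not cure this.

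The trial's own screening shows that a documented SUD and moderate or severe OUD are different populations. The recruitment list was drawn on documented SUD, yet among women then interviewed the joint most frequent reason for ineligibility in Table 3 was "Does not meet DSM-5 criteria for moderate to severe opioid use disorder", with 68 women.

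At stake is the Aim 2 estimate. If the added comparators rarely overdose on opioids, a real benefit is understated, and an ineffective programme could look harmful.

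**Working it through.** **Inputs from the article**

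- Women completing the pre-screen interview: 140. Ineligible afterwards: 79. Eligible: 140 − 79 = 61, as the article states.
- Not meeting moderate or severe OUD: 68. Reasons are multiple-response, but each woman counts once for a given reason.
- Share meeting the criterion: f = (140 − 68)/140 = 72/140 = 0.514.
- Annual overdose rates in the power section: 20% and 25%, with 100 women per group.
- Risk ratio (RR) that the power section cites from other programmes: 0.4.

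**Assumptions, not in the documents**

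- f = 0.514 also holds in the comparison counties.
- r is the opioid-overdose risk of comparators without moderate or severe OUD, relative to those with it. It is varied from 0 to 0.5.
- No adjustment, and no other difference between the groups.

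**Formula**

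Comparator risk relative to OUD women: D = f + (1 − f)r = 0.514 + 0.486r.

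Apparent RR = true RR / D.

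| r | D | true 0.50 appears as | true 0.40 appears as | true 1.00 appears as |
|---|---|---|---|---|
| 0 | 0.514 | 0.97 | 0.78 | 1.94 |
| 0.2 | 0.611 | 0.82 | 0.65 | 1.64 |
| 0.25 | 0.636 | 0.79 | 0.63 | 1.57 |
| 0.5 | 0.757 | 0.66 | 0.53 | 1.32 |

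**Crude power for a true halving** (two-sided 5% test of two proportions, 100 per group, no clustering, the annual rates taken as the risk in OUD women)

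- Comparator all OUD: 51% (0.20 v 0.10) and 62% (0.25 v 0.125).
- f = 0.514, r = 0.5: 19% and 24%.
- f = 0.514, r = 0.25: 9% and 10%.
- f = 0.514, r = 0: about 3% at both rates.

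This simple test does not reproduce Table 4: at zero clustering, 0.20 v 0.095 gives 55% power, not 80%. Table 4 comes from a simulation that is not described in detail. That is a separate matter, and the dilution ratios above do not depend on it.

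**Sensitivity to f**

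The article expects at least 40% of all women released to the pilot counties to have an opioid-abuse history. With f = 0.40, a true 0.50 appears as 1.25 (r = 0), 0.91 (r = 0.25) or 0.71 (r = 0.5).

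**Opposing selection**

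Suppose selection into ROAR multiplies participants' risk by s regardless of treatment. The apparent RR is then s × true RR / D, and the two biases cancel when s = D, that is s = 0.51, 0.61 or 0.76 at r = 0, 0.2 or 0.5.

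**Pool left under an opioid-specific rule**

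60 releases a month × 18 months × 0.5 outside the pilot counties = 540. Applying 40% to 50% gives 216 to 270. From the article's rounder total of 1000 releases, 500 × 0.40 to 0.50 = 200 to 250. The 50% comes from the Background, which reports that "roughly half of women entering prison in Oregon used heroin, street methadone, or other opioids in the 12 months prior to incarceration".

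**The case against.** The best defence is that the documents show a conflict, not a settled SUD comparator. The Discussion says OUD, and a condensed article may leave the exact selection rule to the full protocol or data request. This stands in part: dilution follows only if the SUD wording governs. But three design and analysis sections carry that wording, and the acknowledgement of residual confounding in the Discussion is written as if the comparators had OUD, so it does not cover this imbalance.

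A reader might infer that the plan is bound to hide a true halving. The documents do not support that. Near-complete masking needs r close to zero, and r is not given. Failing the moderate-or-severe threshold does not exclude mild OUD, so the 68 cannot be taken as women with only alcohol or stimulant problems. The 51% share comes from women referred for interview in the pilot counties. At r = 0.5 the effect is attenuated, not hidden. With power of only 51% to 62% before any dilution, a null result could not be put down to dilution alone.

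A reader might also infer that the primary model omits substance-abuse treatment need and so cannot repair the imbalance. The model's covariate list is open-ended, and two other sections say this variable is adjusted for, so it belongs to the plan and may recover part of the bias. It is not opioid-specific, however, and cannot be relied on to remove it.

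Finally, the net direction of bias is uncertain. Participants must be willing to start naltrexone before release and to establish community care, and some severely ill women are excluded. Either may lower risk in the ROAR arm. This stands.

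**Conclusion.** The inconsistency is real and must be resolved: the ROAR arm is defined by moderate or severe OUD, and the comparator by SUD in three sections and by OUD in one. If the SUD wording is followed, this imbalance by itself moves the estimate toward the null or apparent harm. Its size is unknown. With a 51% OUD share and r between 0 and 0.5, a true RR of 0.50 appears between 0.97 and 0.66 before adjustment. Both the share's transfer to other counties and r are assumptions. The net bias may be smaller, or reversed, if selection into ROAR favours lower-risk women, but an unmeasured offset is no reason to leave a known imbalance in the comparator's definition.

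**What to change.** 1. Define the comparator by one opioid-specific administrative criterion: opioid use in the 12 months before incarceration from prison intake data, an OUD diagnosis in Medicaid claims, or both.
2. Use that definition in Aim 2, Limited Administrative Dataset, Sample Size and Power, and the Discussion.
3. In a sensitivity analysis, apply the same administrative rule to ROAR women, so that both groups pass an identical filter.
4. Name substance-abuse treatment need explicitly among the covariates of the primary overdose model.

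The cost is a changed selection rule in a data request that already draws on corrections and Medicaid records. There are three drawbacks. Administrative flags only approximate moderate or severe OUD: reported use is not a diagnosis. A claims-based flag may select women in contact with care, whose risk may differ. The pool shrinks to roughly 216 to 270 of about 540 women before exclusions, if the 40% to 50% shares hold outside the pilot counties. Neither share is an OUD rate, but even the lowest figure above, 200, would have to halve before reaching the 100 required.
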